#### Emergency unblinding {17b}

In this study where researchers are aware of the patients’ treatment status, emergency unblinding is typically not necessary for the researchers. However, it may be required in rare instances where the patient’s safety or well-being is at risk. The decision to unblind a patient will be made by the principal investigator in consultation with the treating physician and an independent data and safety monitoring board. An independent, unblinded investigator who is not involved in the patient’s care or data analysis will carry out the unblinding process, confirming the patient’s identity and the reason for unblinding on the case report form. The study team will review the unblinding and make any necessary adjustments to the patient’s treatment plan or report adverse events to regulatory authorities. It is important to limit the use of emergency unblinding and minimize its impact on the study results.

### Data collection {18a}

#### Trial procedures and evaluations

Patients with FS accompanying MRI diagnoses as rotator cuff injury are randomly divided into two groups: the trial group (with manipulation under brachial plexus block anesthesia as the main intervention) and the control group (with intra-articular steroid injection as the main intervention). All patients included in this study will undergo a program of shoulder exercises, normally commencing within 24 h after the corresponding intervention, with three sessions per day for 2 weeks. The data will be collected before the intervention, 1 day, 2 weeks, 4 weeks, 12 weeks, and 24 weeks after the intervention. Because of the physical examination involved, all follow-ups will be done in the outpatient or inpatient department of the hospital. The investigators used a Case Report Form (CRF) to collect real-time clinical data from the subjects, and any modifications to a CRF will be signed and dated. The collection of outcome data is accomplished through clinical evaluations that are conducted by either a trained practitioner, an orthopedic physician, or a resident in the orthopedic inpatient or outpatient setting. All personnel will undergo training to ensure data quality. The subjects’ data will be securely stored at a designated location. The information collected during the research will be treated as confidential and accessible only to the researchers. The schedule of enrolment, interventions, and assessments is depicted in Fig. 1.

**Fig. 1 Fig1:**
[figure not shown]
Trial flowchart

### Retention {18b}

Due to the nature of this study, since the main treatment is done all at one time, its adherence is guaranteed. The follow-up time points in this study are 1 day, 2 weeks, 4 weeks, 12 weeks, and 24 weeks after the patients received the treatment. Because of the physical examination involved, all follow-up time points must be completed by the patients at the hospital’s outpatient or inpatient departments. The study staff will contact participants over the phone or on WeChat to supervise their home exercise program and to make appointments before their scheduled follow-up examinations. Finally, participants will receive reimbursement for their time and transportation as 50 yuan for each visit.

### Data management {19}

The investigators used a Case Report Form (CRF) to collect real-time clinical data from the subjects. To ensure the objectivity of the clinical data, all subjects in this study are followed up and observed by the same investigator. The CRF form needs to be filled and reviewed at the same time when examining the patients. When finally entering the data, double entry and cross-checking will be used, and data will be periodically and randomly checked by data management staff to ensure the accuracy. A special statistical staff at Shanghai University of T.C.M. will analyze the data unaware of the allocation.

## Statistical methods

### Outcomes {20a}

The data will undergo encoded analysis and various patient details, such as their baseline information, range of motion, CMS, VAS, MPQ, PPI, duration of symptoms before treatment, and past histories, will be compared and summarized between the groups. The outcome variables of all patients will also be summarized by treatment group and time, following descriptive statistics such as the number of patients, mean and standard deviation (or median and interquartile range) for continues variables, and relative frequencies for categorical variables. The number of participants included in each analysis will be reported, and we will adhere to the intention to treat principle regarding the group assignment.

Differences between the various treatments will be calculated using one-way ANOVA statistics; the follow-up data of each group will be statistically analyzed using ANOVA of repeated measures if they conformed to normal distribution and chi-square, and if they do not, the rank sum test will be used; logistic regression will be used to analyze the correlation between each treatment method and the efficacy. The study will categorize complications by types, such as infection, post-operative pain, nerve, blood vessel, tendon, or bone injury, and count them overall. Poisson regression analysis will be used with corrections for overdispersion when appropriate. The impact of treatment on complication rates will be expressed as MUA to intra-articular injection rate ratios. The safety of the treatment will be evaluated by identifying and summarizing any adverse events that occur during the study. All treatment effects will be reported with their 95% confidence intervals and *p*-values. The statistical analysis will be conducted using the IBM SPSS statistical package (version 25.0).

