**Methods:**

A parallel, single-blinded, multi-center randomized controlled trial of 320 patients will be conducted at three hospitals of China. Eligible patients with frozen shoulder and rotator cuff injury or tear diagnosed by MRI will be randomly assigned to, in equal proportions, the manipulation under anesthesia group and the intra-articular steroid injection group via a central randomization system, undergoing a corresponding operation on day one and a sequent physical exercise for 14 days. The primary outcome is the comprehensive efficacy evaluation (total effective rate) and the change of Constant-Murley Score. Outcome assessors and data analysts will be blinded, and participants will be asked not to reveal their allocation to assessors.

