##### Post-procedural physiotherapy (PPP)

Patients from both groups will initiate a 14-day functional exercise, starting on the first day after the intervention treatment. A uniformly and strictly trained physician guides the first functional exercise of the patients until the patients and their accompanying family members have mastered the correct exercise method. They can record relevant videos, and family members can assist and supervise patients in the initial exercise stage. Physicians follow up with patients regularly to ensure the standardization and correctness of exercise posture.

The specific methods are as follows:①Forward elevation: The patient stands facing a wall with their feet shoulder-width apart and toes touching the wall. The fingers of the affected arm are spread out and placed on the wall. Slowly elevate the arm along the wall until the limit of pain tolerance is reached. The unaffected arm can assist in lifting the affected arm, or another person can push the scapula of the affected side from behind to help raise the arm to the maximum position.②Forward flexion with shoulder support: The affected shoulder is flexed to 90° with the elbow flexed. The palm of the unaffected hand is gradually placed on the elbow, moving it towards the midline to bring the affected arm to rest on the opposite shoulder joint.③Extension with internal rotation: The patient sits or stands with the palm of the affected hand facing backward and extends the shoulder joint. Within the limit of pain tolerance, gradually rotate and adduct the affected arm while bending the elbow until the fingers touch the opposite scapula. The unaffected hand can assist the affected hand in completing the exercise.

Repeat the above movements after the patient’s pain is relieved. Perform three sets of each exercise, three times per day.

The ROM, CMS, MPQ, VAS, and PPI numbers or scores will be collected at 1 day, 2 weeks, 4 weeks, 12 weeks, and 24 weeks after the intervention. Additionally, imaging examinations will be conducted during the 24-week visit. Due to the nature of the physical examinations required, all follow-up time points must be completed by the patients at the hospital’s outpatient or inpatient departments.

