### Allocation {16a} {16b}{16c}

Eligible subjects who meet the test and research criteria will be randomly assigned into two groups, the trial group and the control group, in a 1:1 ratio. The random number table used for the randomization process is generated by statisticians at Shanghai University of T.C.M. and is not accessible to anyone else involved in the study. The randomization will be stratified by participating site and done in blocks of four. Each subject can only register and be randomized once, and their information cannot be deleted from the database. The clinicians will identify patients with frozen shoulder and confirm their eligibility using a CRF completed by a designated individual in the shoulder team. The recruiting clinician will then contact the statistical staff for randomization. The hospital staff will be informed of the allocation, but not the patient. The patient will be fully informed about the allocated therapy and given an information sheet to review before deciding to consent, which can take up to a week. If the patient does not consent, their reason for not doing so will be briefly recorded in a CRF. Those who consent will complete baseline forms and receive further treatments.

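### The stated analysis of CMS change is unadjusted for baseline and site and is chosen by a distribution check, so it is valid but less precise than one pre-set adjusted between-arm model

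*Protocol article*

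**What the plan says.** The abstract (Methods) makes CMS change one of two primary outcomes: "The primary outcome is the comprehensive efficacy evaluation (total effective rate) and the change of Constant-Murley Score". CMS is measured before treatment (Trial design {8}; Table 1), and the scores "will be collected at 1 day, 2 weeks, 4 weeks, 12 weeks, and 24 weeks after the intervention" (Post-procedural physiotherapy).

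For the analysis, Outcomes {20a} states three things in one sentence:

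- Between treatments: "Differences between the various treatments will be calculated using one-way ANOVA statistics".
- Over time: "the follow-up data of each group will be statistically analyzed using ANOVA of repeated measures if they conformed to normal distribution and chi-square".
- Fallback: "if they do not, the rank sum test will be used".

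The same section adds that "All treatment effects will be reported with their 95% confidence intervals", together with p-values. On randomisation, Allocation {16a} {16b}{16c} says: "The randomization will be stratified by participating site and done in blocks of four".

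The ANOVA sentence does not name CMS, but nothing else in the section suits a continuous outcome. No baseline covariate, site term, arm-by-visit contrast or primary CMS visit is given.

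**The concern.** This is more than detail left to an analysis plan. A one-way ANOVA has a single factor, so naming it excludes baseline and site by construction, and an analysis plan that added them would depart from the published method. Four consequences follow.

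1. Baseline CMS is collected and site is the stratification factor, but neither enters as a covariate. The precision they could supply is lost.
2. The repeated-measures analysis is described for each group, with no contrast between arms. The Background cites work calling the condition self-limiting, and both arms exercise for 14 days, so improvement over time is to be expected in both and would not show superiority.
3. The observed data decide which method is used for a primary outcome, and the condition as worded cannot be applied: it is unclear what conforming to chi-square means for a continuous score.
4. The fallback answers a different question. A rank sum test compares two independent samples, so it does not replace a repeated-measures analysis, and it returns a p-value rather than a mean difference with a confidence interval.

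**Working it through.** **Plan's own figure.** There is none for CMS. The 160 per group in Sample size {14} rests on the total effective rate, so no CMS calculation can be reproduced.

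**Inputs from the protocol.** 160 per arm and 10% dropout (Sample size {14}), hence 160 × 0.9 = 144 per arm evaluable; five follow-up visits; randomisation stratified by site across three hospitals.

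**Assumed inputs, not in the protocol.** Correlation ρ between baseline and follow-up CMS of 0.3, 0.5 or 0.7; equal SD at baseline and follow-up; share s of outcome variance due to site of 2%, 5% or 10%; a missed-visit rate q of 2%, 3% or 5%, independent across visits.

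**Step 1: baseline.** At one visit, the variance of the arm difference relative to a one-way ANOVA of follow-up scores is:

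- follow-up score: 1
- change score: 2(1 − ρ)
- baseline-adjusted (ANCOVA): 1 − ρ²

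The ratio of ANCOVA to change score is (1 − ρ²) / [2(1 − ρ)] = (1 + ρ)/2.

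| ρ | Change score | ANCOVA | Reduction vs change | Reduction vs follow-up score |
|---|---|---|---|---|
| 0.3 | 1.40 | 0.91 | 35% | 9% |
| 0.5 | 1.00 | 0.75 | 25% | 25% |
| 0.7 | 0.60 | 0.51 | 15% | 49% |

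The last entry is 1 − 0.51 = 49%; the remaining variance is 51% of that for follow-up scores.

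The direction does not need equal SDs. If the baseline SD is k times the follow-up SD, the change-score variance is 1 + k² − 2kρ, which exceeds 1 − ρ² by (k − ρ)², never a negative amount.

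**Step 2: what this means at 144 per arm.** The smallest difference detectable with 80% power at two-sided 5%, in follow-up SDs, is (1.96 + 0.842) × √(2f/144), where f is the relative variance above.

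- Follow-up score: 0.330
- Change score: 0.391, 0.330, 0.256 at ρ = 0.3, 0.5, 0.7
- ANCOVA: 0.315, 0.286, 0.236

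Power for a difference of 0.33 SD is 80% with follow-up scores; 66%, 80% and 95% with change scores; and about 84%, 90% and 98% with ANCOVA.

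**Step 3: site.** Leaving site out inflates the standard error by 1/√(1 − s): 1.010, 1.026 and 1.054 for s = 2%, 5% and 10%. This is about 1% to 5%, and in the conservative direction.

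**Step 4: missed visits, on one reading only.** If the repeated-measures ANOVA is the joint between-arm model and is run in its conventional complete-case form, the share of patients lost is 1 − (1 − q)⁵:

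- q = 2%: 9.6%, leaving 289 of 320
- q = 3%: 14.1%, leaving 275 of 320
- q = 5%: 22.6%, leaving 248 of 320

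Misses clustered in the same patients would cost less. If the repeated-measures ANOVA is run within each arm, none of this loss touches the comparison between arms.

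**The case against.** The strongest defence is that the plan does contain a valid comparison. With two arms, a one-way ANOVA at a visit gives a mean difference with a confidence interval and uses everyone measured at that visit. A reader might infer that no between-arm estimate can be obtained. The text does not support that: a difference is available at each visit, and what is missing is only the designation of one.

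A reader might also infer a contradiction with intention to treat. The commitment is narrower: "we will adhere to the intention to treat principle regarding the group assignment". It concerns analysis as allocated, and missing outcomes do not breach it.

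Nor can the within-arm reading and the loss of patients both be charged. Either the repeated-measures ANOVA does not compare arms, and complete-case deletion leaves the comparison untouched, or it does compare arms, and the deletion matters. The wording allows both readings.

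On precision, baseline is not wholly ignored if the outcome is CMS change, since it enters by subtraction. The 35% gain applies only against that comparator; against follow-up scores at the same correlation it is 9%. The entry limits restrict range of motion, whereas 60 of the 100 CMS points (pain 15, daily living 20, strength 25) are not movement, so the protocol does not point to any particular correlation.

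Finally, nothing says that within-arm significance will be offered as evidence of efficacy, and the absence of covariates from the logistic model is mere silence.

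All of these limits stand. They leave untouched the one-factor method, the data-dependent switch and the mismatch between the rank test and the promised interval.

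**Conclusion.** The point holds in limited form. For CMS change, the protocol fixes an analysis that is valid but inefficient: no baseline covariate, no site term, no stated arm-by-visit contrast, a method chosen by a distribution check, and a fallback that gives no mean difference for the promised interval.

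The size depends on a correlation the protocol does not give. Over 0.3 to 0.7, with equal SDs, baseline adjustment removes 35% down to 15% of the variance of change scores, or 9% up to 49% of the variance of follow-up scores (at 0.7 the adjusted variance is 51% of the unadjusted). Adjustment is at least as precise at every value. The contribution of site is minor. A loss of around 14% of patients is conditional twice over: on the repeated-measures ANOVA being the joint model, and on an assumed 3% independent miss rate per visit.

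It would go too far to call the planned comparison biased, incompatible with the intention-to-treat statement, or incapable of producing a between-arm estimate. This is an improvement the sponsor should make, not an error that invalidates the trial.

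**What to change.** In Outcomes {20a}, replace the ANOVA and rank-test sentence, for CMS and the other continuous outcomes, with one pre-set between-arm model: a linear mixed model for repeated measures (SPSS MIXED) with arm, visit, arm-by-visit, baseline value and site. ANCOVA with arm, baseline and site at the named visit is an acceptable simpler form. Report the arm difference at one visit named in advance, with its 95% confidence interval and p-value.

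Remove the distribution check as a gate and keep the rank sum test only as a sensitivity analysis. State that change within an arm is descriptive and will not be used as evidence of efficacy. As a recommendation rather than a correction, include site in the logistic model for the total effective rate.

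The cost is wording only: the data are already collected, the software is already chosen, and no visit or patient is added. The change should be dated and made before outcome data are analysed by arm.

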### Explanation for the choice of comparators {6b}

Intra-articular steroid injection is a common treatment of FS [37], providing short-term benefits [37, 46, 47], and also proving effective for rotator cuff tear [48]. It is an effective, common, affordable treatment with little direct transformation to the shoulder structure, that is why we choose it as our control group’s treatment.

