##### Safety evaluation

Adverse effects, including humeral shaft fracture, glenoid fracture, shoulder dislocation, complex regional pain syndrome, neurovascular lesions, and infection, will be recorded at any time during the trial. In addition, an MRI of the glenohumeral joint and a musculoskeletal ultrasound of the shoulder will be performed 6 months after treatment to assess the safety effects of the MUA on the rotator cuff.

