## Discussion

In this study, we propose to compare the efficacy of manipulation under anesthesia versus intra-articular steroid injection in the treatment of patients diagnosed with rotator cuff injury with frozen shoulder. We expect that the MUA group will have a superior outcome compared to the intra-articular steroid injection group in terms of the primary outcome measure. If our hypothesis is confirmed, this study could lead to a change in the standard of care for patients with rotator cuff injury and frozen shoulder and provide a new treatment option with fewer side effects and better outcomes.

It is important to note that this study has several limitations. First, the study is single-blinded due to the nature of the interventions, meaning that the physicians will not be blinded to the treatment group, which could introduce bias. Second, the study is limited to patients diagnosed with rotator cuff injury with frozen shoulder based on MRI findings and may not be generalizable to patients with other types of shoulder injuries. Finally, the study is limited to 24 weeks of follow-up, and longer-term outcomes are not evaluated.

In conclusion, this study protocol outlines a randomized controlled trial that will compare the efficacy of manipulation under anesthesia versus intra-articular steroid injection in the treatment of patients diagnosed with rotator cuff injury with frozen shoulder. The study has the potential to provide important insights into the treatment of this common condition and could lead to improvements in patient care.

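### A Poisson rate ratio is the only effect measure planned for complications, and it suits fracture and dislocation badly: undefined if the control arm has none, diluted if all complications are pooled

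*Protocol article*

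**What the plan says.** The safety list in the Safety evaluation section covers "Adverse effects, including humeral shaft fracture, glenoid fracture, shoulder dislocation, complex regional pain syndrome, neurovascular lesions, and infection". In Statistical methods, Outcomes {20a}, the handling of complications is set out in four steps:

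- Classification: "The study will categorize complications by types, such as infection, post-operative pain, nerve, blood vessel, tendon, or bone injury, and count them overall".
- Model: "Poisson regression analysis will be used with corrections for overdispersion when appropriate".
- Effect measure: "The impact of treatment on complication rates will be expressed as MUA to intra-articular injection rate ratios".
- Reporting: "All treatment effects will be reported with their 95% confidence intervals and *p*-values".

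The same section adds a descriptive commitment: "The safety of the treatment will be evaluated by identifying and summarizing any adverse events that occur during the study".

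The text does not say whether the model is fitted to each type or only to the overall count. It does not name the test or interval method, and it gives no complication rate for either arm.

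Two other places bear on which arm will have structural events. The section on the choice of comparators {6b} calls the injection an "affordable treatment with little direct transformation to the shoulder structure". The description of the manipulation under Interventions {11a} tells the operator to guard against dislocation and names fracture as a possible result of poor technique.

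**The concern.** Safety is half of the stated objective (Objectives {7}), and verifying the safety of MUA in patients with cuff injury is a listed aim (Additional analyses {20b}). The harms that matter most for that question are mechanical. By the protocol's own account they belong to the manipulation far more than to the injection.

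A ratio of rates works poorly for such harms. If the control arm has no event of a given type, the denominator is zero. If that is avoided by pooling all complications, a handful of structural injuries is added to a larger number of minor events. Either way, the one comparative statistic the plan commits to may say little about the harm of interest, or may sit beside the raw counts and point the wrong way.

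**Working it through.** **Inputs.** The protocol gives no complication figure to reproduce. Arm size comes from Sample size {14}: 160 per group with 10% dropout, so 160 × 0.9 = 144. All event rates and counts below are assumptions.

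**Step 1: how likely is an empty control arm?** P(no events) = (1 − p)^n.

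| Assumed control risk p | n = 144 | n = 160 |
|---|---|---|
| 0.2% | 75% | 73% |
| 0.5% | 49% | 45% |
| 1% | 24% | 20% |
| 2% | 5% | 4% |

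An empty control arm is more likely than not only when p is below about ln 2 / 144 = 0.48%. It is therefore plausible for fracture or dislocation after an injection, but not established.

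**Step 2: ratios fitted by type, k MUA events versus 0, 144 per arm.** The maximum-likelihood ratio is (k/144)/(0/144), which is infinite. Fitted numerically at k = 6, the Poisson log ratio stops at about 22.4 with a standard error of about 17,984. So z = 22.4/17,984 ≈ 0.001 and the Wald p is 0.999. For significance the standard error would have to fall below 22.4/1.96 = 11.4, so rescaling it for overdispersion changes nothing of substance.

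The other tests use the same data. The likelihood-ratio statistic is 2k ln 2 on 1 df (for k = 6, 8.32), and the exact conditional p is 2 × 0.5^k.

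| MUA vs injection | Wald p | Likelihood-ratio p | Exact conditional p | Fisher p |
|---|---|---|---|---|
| 3 vs 0 | 0.999 | 0.041 | 0.25 | 0.247 |
| 6 vs 0 | 0.999 | 0.004 | 0.031 | 0.030 |
| 8 vs 0 | 0.999 | 0.0009 | 0.008 | 0.007 |
| 10 vs 0 | 0.999 | 0.0002 | 0.002 | 0.002 |

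Lower limits for the ratio at 6 vs 0 do exist: 1.18 exact (q = 0.025^(1/6) = 0.541; q/(1 − q)) and 2.65 by profile likelihood (q = exp(−3.84/12) = 0.726; q/(1 − q)). The point estimate and upper limit are infinite under every method.

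**Step 3: only the overall count is modelled.** Suppose 6 structural injuries with MUA and none with injection, plus 30 other complications in each arm. The ratio is 36/30 = 1.20. The standard error of its log is √(1/36 + 1/30) = 0.247, so the 95% interval is 0.74 to 1.95 and p = 0.46. With 20 other complications under MUA, 26/30 = 0.87, which favours MUA despite 6 versus 0 structural injuries.

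**Step 4: what a risk difference would show.** For 6/144 versus 0/144 the difference is 4.2 percentage points. Wilson limits are 1.92% to 8.79% for 6/144 and 0% to 2.60% for 0/144. The Newcombe score interval is then 4.17 − √((4.17 − 1.92)² + 2.60²) = 0.7 to 4.17 + √((8.79 − 4.17)² + 0²) = 8.8 points. It is finite and readable. With no events in 144, the exact upper limit is 1 − 0.025^(1/144) = 2.5%, so even a clean arm does not exclude a risk of that size.

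**The case against.** The strongest reply is that the failure needs choices the protocol never makes.

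First, the text says complications are counted overall. The natural reading may be a single model of that count, which includes infection and post-operative pain and so is unlikely to be empty in the control arm. This is a fair reading, but it leads to Step 3, where the ratio is finite and the structural harm is diluted.

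Second, no test is named. The p-value near 1 is a property of the Wald test, not of Poisson regression or the rate ratio. This stands. A reader might infer that the stated method can never show an excess however many MUA events occur, but the protocol does not support that: a likelihood-ratio test of the same model falls below 0.05 from 3 versus 0.

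Third, a reader might infer that structural harms will probably be absent in the control arm. No complication rate is given, so that is only an assumption.

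Fourth, harm would not be concealed. Events are to be summarised, adverse reactions are to be described and compared between groups (Analysis population and missing data {20c}), and the monitoring board reviews safety data every 3 months. This also stands. Nor does the protocol say that p above 0.05 will be taken as proof of safety.

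Finally, zero-cell handling is commonly left to an analysis plan, which is not shown. That is true of the test and interval method. The effect measure itself, however, is fixed in the protocol, and it is the effect measure that fits rare one-sided harms poorly.

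**Conclusion.** The point holds in a limited form. The protocol commits to one comparative measure for complications, and on either reading of its text that measure is weak for structural harms. Fitted by type with an empty control cell, it has no finite estimate or upper limit, and default Wald output would give p of about 0.999 at 6 versus 0 against Fisher's 0.030. Fitted to the overall count, 6 versus 0 structural injuries can appear as a ratio of 1.20 (0.74 to 1.95).

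This rests on assumed event counts and on control risks of roughly 1% or less for the structural types. It does not show that the trial would miss harm, because the raw events will be reported. When events are very few, no method helps much: at 1 or 2 versus 0, none of the tests computed reaches 0.05.

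The Discussion's hope that a confirmed hypothesis could "provide a new treatment option with fewer side effects and better outcomes" is a separate, minor matter of wording. Success on the efficacy outcome would not by itself support the part about side effects, but that sentence does not bear on the choice of model.

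**What to change.** In Statistical methods, Outcomes {20a}, or in the analysis plan:

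- Keep the Poisson rate ratio for the overall complication count, and say that this is where it applies.
- For each structural complication type, and for any structural complication, report the number of patients with an event in each arm and the MUA-minus-injection risk difference with an exact or score 95% interval. If a p-value is given, use Fisher's exact test.
- State that Wald tests and intervals will not be used where a cell is empty.
- State that a non-significant difference will not be read as evidence of safety, and that the upper confidence limit will be reported so readers can see what size of excess remains possible.

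The cost is a few sentences and one extra standard table, with no new data. The drawback is that intervals for rare events will be wide, which reflects what a trial of this size can show.
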